#### Continuous outcomes

Because treatment outcomes are measured at 6, 12, and 18 months, treatment effects may not be consistent across time points. In the case of a constant treatment effect across time, the detectable difference depends on the intraclass correlation coefficient (ICC) between measurements taken from a given participant. Since 160 participants per arm are assumed after attrition, and there are 3 measurements per participant, the effective sample size (ESS) per arm is 3*160/VIF, where VIF is the variance inflation factor 1 + (p-1)*ICC. In this formula, p is the average number of observations per participant. Table 1 shows the minimal detectable constant treatment effect under a range of values for the ICC when testing at a power of 80%. The detectable differences are given in terms of the standard deviation of the error term of the model. Thus, if the ICC is 0.3, the current study has 80% power to detect a shift of 0.229 standard deviations between the treatment arms, a small effect size per Cohen [104]. Power calculations displayed in Table 1 assume approximately consistent effects of treatment across measurements. However, correlations between more distal time points are generally lower than more proximal time points. Thus, calculations presented in Table 1 represent a worst-case scenario. We further computed power for detecting an average intervention difference of 0.3 when the effect varies across time points, specifically, with a shift of 0.1 at 6 months, 0.3 at 12 months, and 0.5 at 18 months. A Geisser-Greenhouse Corrected F Test was used for testing the intervention effect. The estimated power for detecting the treatment effect was 99%, 96%, and 91% for ICC values of 0.1, 0.3, and 0.5, respectively. It is important to note that the presented case of a 0.1, 0.3, and 0.5 increasing difference across time points produces exactly the same power as that of a 0.5, 0.3, and 0.1 decreasing difference across those time points.

**Table 1 T1:** Minimal detectable difference with constant effect

**ICC**	**VIF**	**ESS**	**Detectable difference**
0.0	1.0	480	0.181
0.1	1.2	400	0.198
0.3	1.6	300	0.229
0.5	2.0	240	0.256
1.0	3.0	160	0.314

Note: ICC = intraclass correlation coefficient; VIF = Variance Inflation Factor; ESS = Estimated Sample Size.

#### Binary outcomes

National data suggest that approximately 5% of the general population of smokers quit each year [105]. However, smokers in HE receive a brief treatment based on national recommendations [22]. Therefore, we estimate that the abstinence rate for HE will be approximately 5%, 10%, and 15% across the three follow-ups (i.e., 10% quit rate per year). Power calculations for correlated binary outcomes are more complex than continuous outcomes, which require simulations. For example, it is not possible to have the same ICC between all pairwise observations. Therefore, the mean of all pairwise ICC values was used as the overall ICC and looked at three potential scenarios based on the simulation of 1000 trials. Using the estimated quit rate for HE of 5%, 10%, and 15% across the three follow-ups, Table 2 shows simulation results for constant, increasing, and decreasing differences between arms for each time point at ICC values of 0.1, 0.3, and 0.5. For cessation induction trials such as this one, the most likely scenario would be increasing differences over time given that 80-90% of smokers will not be motivated to quit at Baseline. Regardless, power is very good for detecting reasonable and meaningful differences between groups under realistic scenarios.

**Table 2 T2:** Simulation results

	**Constant differences**				**Increasing differences**				**Decreasing differences**		
	**6 months**	**12 months**	**18 months**		**6 months**	**12 months**	**18 months**		**6 months**	**12 months**	**18 months**
**HE**	0.05	0.10	0.15	**HE**	0.05	0.10	0.15	**HE**	0.05	0.10	0.15
**MAPS**	0.15	0.20	0.25	**MAPS**	0.10	0.20	0.30	**MAPS**	0.20	0.20	0.20
**difference**	0.10	0.10	0.10	**difference**	0.05	0.10	0.15	**difference**	0.15	0.10	0.05
**ICC**	**power**	**95% CI**		**ICC**	**power**	**95% CI**		**ICC**	**power**	**95% CI**	
**0.10**	0.99	0.98**-**1.00		**0.10**	0.99	0.98	1.00	**0.10**	0.99	0.98**-**1.00	
**0.30**	0.94	0.93**-**0.95		**0.30**	0.95	0.94	0.96	**0.30**	0.98	0.97**-**0.99	
**0.50**	0.79	0.76**-**0.82		**0.50**	0.84	0.82	0.86	**0.50**	0.98	0.97**-**0.99	

Note: HE = Health Education; MAPS = Motivation And Problem Solving; ICC = intraclass correlation coefficient; CI = confidence interval.

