### Data analysis

Primary outcomes used to evaluate the efficacy of the MAPS intervention (Aim 1) are smoking status, servings of fruits and vegetables, and both self-reported and objectively measured physical activity assessed at the 6, 12, and 18 months. Because the primary outcomes and mechanisms include repeated measurements that are correlated within subjects, the data analytic approach utilizes generalized linear mixed model regression GLMM; [92,93]. Model diagnostics will be used to determine and address the form of the covariances, transformations, collinearity, and influential observations. GLMM parameter tests will be conducted using Wald statistics, and will be adjusted for multiple comparisons where appropriate. Adjustments for multiple comparisons will be made according to the method of Westfall and Young [94]. In this approach, the correlations among the dependent variables are used to adjust the critical values of the individual tests to ensure that the probability of a Type I error across a set of tests does not exceed the chosen alpha level. This approach has the advantage of maintaining the chosen Type I error rates while at the same time providing a less conservative adjustment than Bonferonni-type procedures.

#### Aim 1

Evaluate the efficacy of a MAPS approach to promoting and facilitating reduction of behavioral risk factors for cancer among high-risk Mexican-origin individuals (overweight/obese smokers). Relative to HE, MAPS is hypothesized to result in positive changes in each of the primary smoking, diet, and physical activity outcomes.

GLMM will be utilized in analyzing the effects of MAPS on the primary outcomes across the 6, 12, and 18-month time points. For the dichotomous outcome, we will assume a logit link and binomial variance function for the GLMM, and parameterize them with blocking on individual nested within treatment condition. Treatment and time will be included, as well as their interaction, with adjustment for relevant covariates as necessary. Time will be treated as a categorical variable. These models test for the main effects of treatment and time, and whether the treatment effect varies over time. For the continuous outcomes, the GLMM analysis will be replaced by linear mixed model (LMM) analysis (i.e., a special case of GLMM in which each outcome variable is continuous).

#### Aim 2

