### Power

All power analyses assume a significance level of 0.05 and a two-sided test and accounts for a potential 20% attrition at all time points (N = 320; 160/group). Three of the outcomes are continuous (servings of fruits and vegetables, METS of physical activity, accelerometer assessed activity). One outcome (smoking status) is dichotomous. Power is expected to be greater for intent-to-treat analyses than the power reported here, which represents completers only analyses. This is because the total number of cases for intent-to-treat analyses will be 400, versus 320 for the completers only analyses. For intent-to-treat analyses, those lost to follow up will be coded as not abstinent.

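### Table 2's smoking power at ICC 0.5 does not match the planned treatment main-effect test: the constant cell (0.79) is too low and the decreasing cell (0.98) too high

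*Protocol article*

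**What the plan says.** The Power section sets the common inputs: "All power analyses assume a significance level of 0.05 and a two-sided test", with an allowance for a "potential 20% attrition at all time points (N = 320; 160/group").

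Under Binary outcomes, the "abstinence rate for HE will be approximately 5%, 10%, and 15% across the three follow-ups". Table 2 then gives simulated power (1000 trials) for "constant, increasing, and decreasing differences between arms for each time point at ICC values of 0.1, 0.3, and 0.5". In the constant scenario the intervention row reads "MAPS 0.15 0.20 0.25". In the increasing scenario it is 0.10, 0.20, 0.30, and in the decreasing scenario 0.20 throughout. The mean difference is 0.10 in all three. On correlation, the section says that "the mean of all pairwise ICC values was used as the overall ICC"; it gives no individual pairwise values and does not name the test that was simulated.

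The Data analysis section (Aim 1) plans a logit mixed model with treatment, categorical time and their interaction, tested by Wald statistics. It adds: "These models test for the main effects of treatment and time, and whether the treatment effect varies over time". The treatment main effect is therefore a separate test from the interaction.

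Under Continuous outcomes, power is computed for an average difference, and an increasing pattern "produces exactly the same power as that of a 0.5, 0.3, and 0.1 decreasing difference across those time points". That is how a test of the averaged effect behaves.

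**The concern.** Two features of Table 2 are hard to square with a test of the averaged treatment effect.

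- **Spread across scenarios.** At ICC 0.5 the stated power is 0.79, 0.84 and 0.98 (constant, increasing, decreasing), although the mean difference is the same. The constant-to-decreasing gap is 19 points.
- **Response to ICC.** The decreasing column hardly moves as ICC goes from 0.1 to 0.5 (0.99, 0.98, 0.98), while the constant column falls from 0.99 to 0.79. The Continuous outcomes section's own variance inflation factor rises from 1.2 to 2.0 over that range, so power for an averaged effect should fall in both.

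Smoking status is a primary outcome, and the article's favourable statement about power for it rests on this table. If the cells belong to another test, the reader is misled about how far power depends on the shape of the effect.

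**Working it through.** **Inputs.** n = 160 per arm and two-sided 0.05 (Power); control rates 0.05, 0.10, 0.15 and the intervention rates above (Table 2); mean pairwise ICC 0.1, 0.3, 0.5. Assumption: equal pairwise correlations first, then other feasible sets with the same mean.

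**Averaged risk difference (1 df).** With s = √[p(1−p)] at each visit, the variance of a participant's mean over three visits is (1/9) ΣΣ ρ·s·s. SE = √[(V_HE + V_MAPS)/160]; z = 0.10/SE.

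At ICC 0.5, V_HE = 0.0573 and:

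- constant: V_MAPS = 0.1051, SE = 0.0319, z = 3.14, power 0.88
- increasing: V_MAPS = 0.1001, SE = 0.0314, z = 3.19, power 0.89
- decreasing: V_MAPS = 0.1067, SE = 0.0320, z = 3.12, power 0.88

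**Averaged log odds ratio (1 df), the marginal analogue of the planned logit test.** At ICC 0.5:

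- constant: (1.210 + 0.811 + 0.636)/3 = 0.886, SE 0.284, z = 3.12, power 0.88
- increasing: (0.747 + 0.811 + 0.887)/3 = 0.815, SE 0.290, z = 2.82, power 0.80
- decreasing: (1.558 + 0.811 + 0.348)/3 = 0.906, SE 0.283, z = 3.21, power 0.89

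**Random-intercept logistic model.** Simulated with correlated binary data (500 trials per cell) at ICC 0.5. The averaged treatment effect with the interaction in the model gives 0.92, 0.85 and 0.93. Without the interaction the model gives 0.88, 0.90 and 0.87.

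**Comparison with Table 2** (equal correlations for the analytic columns):

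| ICC | Scenario | Stated | Averaged risk difference | Averaged logit | 3-df joint test (risk difference) |
|---|---|---|---|---|---|
| 0.1 | constant | 0.99 | 0.98 | 0.98 | 0.95 |
| 0.1 | increasing | 0.99 | 0.98 | 0.95 | 0.95 |
| 0.1 | decreasing | 0.99 | 0.98 | 0.98 | 0.99 |
| 0.3 | constant | 0.94 | 0.94 | 0.94 | 0.88 |
| 0.3 | increasing | 0.95 | 0.945 | 0.88 | 0.88 |
| 0.3 | decreasing | 0.98 | 0.94 | 0.95 | 0.97 |
| 0.5 | constant | 0.79 | 0.88 | 0.88 | 0.80 |
| 0.5 | increasing | 0.84 | 0.89 | 0.80 | 0.83 |
| 0.5 | decreasing | 0.98 | 0.88 | 0.89 | 0.97 |

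**What reproduces.** The averaged risk difference comes within a point of the whole ICC 0.1 row and of the constant and increasing cells at ICC 0.3. The increasing cell at ICC 0.5 (0.84) agrees with the mixed model (0.85).

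**What does not.** Constant and decreasing at ICC 0.5 fit none of the averaged tests. Decreasing at ICC 0.3 is high on the marginal scale; the mixed model with interaction gives 0.96 there, so that cell is the weaker part of the finding.

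**Cross-check with the article's own formula.** Effective sample sizes per arm are 480/1.2 = 400, 480/1.6 = 300 and 480/2.0 = 240. A two-proportion test of 0.10 against 0.20 then has power 0.98, 0.93 and 0.87.

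**Unknown pairwise correlations.** Over feasible sets with mean 0.5, the two averaged tests stay within 0.87 to 0.89 (constant) and 0.87 to 0.90 (decreasing).

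**Simulation noise.** With 1000 trials the standard error is √(0.79·0.21/1000) = 0.013 and √(0.98·0.02/1000) = 0.004. The nearest constant value, 0.87, is 0.08/0.013, about 6 standard errors from 0.79. The nearest decreasing value, 0.932, has its own error √(0.932·0.068/500) = 0.011. The combined error is 0.012, so 0.048/0.012 is about 4. The table's intervals (0.76 to 0.82 and 0.97 to 0.99) exclude both.

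**The case against.** The article is condensed and does not name the simulated test, and simulation settings are often left to a fuller document. That is fair. The point is not that they are missing, but that printed figures do not fit the test the same article plans.

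Either cell alone could come from some other test. A common odds ratio without the interaction, weighted for efficiency, gives about 0.79 for constant under equal correlations. An optimally weighted risk difference can reach 0.93 to 0.99 for decreasing, depending on the correlations. Neither is the planned averaged effect. Under equal correlations the common-odds-ratio test gives only 0.63 for decreasing, and at most 0.92 over the correlations searched, so it cannot supply both cells.

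A reader might infer that the three scenarios must have equal power because each averages 0.10. The documents do not support that. It nearly holds for risk differences, but the planned link is logit, where equal risk differences are unequal effects: the averaged-logit figures are 0.88, 0.80 and 0.89. Some spread is expected; 0.79 against 0.98 is not.

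A reader might also take 0.98 as the 6-month contrast alone (5% against 20%, power 0.98). That contrast gives 0.85 for constant and 0.40 for increasing, so it cannot explain the table.

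Finally, most cells stand or nearly so, and the scenario the article calls most likely, increasing, agrees with the mixed model at ICC 0.5.

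**Conclusion.** The point holds in limited form. At ICC 0.5 the planned main-effect test has power of about 0.87 to 0.92 for constant differences (stated 0.79, understated by 8 to 13 points). For decreasing differences it has about 0.87 to 0.93 (stated 0.98, overstated by 5 to 11 points). The 3-df test fits the ICC 0.5 row but gives 0.88 and 0.88 where the ICC 0.3 row has 0.94 and 0.95. No single test tried reproduces all nine cells.

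This rests on 160 per arm, two-sided 0.05, the stated rates, and mean pairwise binary correlation as the meaning of ICC.

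It would be wrong to conclude that smoking is underpowered or that 400 participants are too few. Main-effect power at ICC 0.5 is about 0.80 or above in every scenario, and one of the two misstated cells errs on the cautious side. Nor does the finding depend on a multiplicity-adjusted level: the article openly computes power at 0.05, and any adjustment is a separate matter. The size of the problem is modest: stated figures for a primary outcome that should be corrected, with no design decision overturned.

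**What to change.** Rerun the Table 2 simulation for the Aim 1 treatment main effect averaged over 6, 12 and 18 months, with the planned logit mixed model, Wald test and stated two-sided 0.05. Name that test beside the table, give the pairwise correlations used in each arm, and replace the cells that differ.

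All nine cells should be rerun. The increasing cells at ICC 0.1 and 0.3 match the risk-difference version but lie above the logit one, so the scale should be settled at the same time. If power for a joint or single-visit test is also of interest, report it separately and label it as such.

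The cost is a small simulation and at most nine replaced numbers. Sample size, design and the planned analysis stay as they are.

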## Discussion

Interventions addressing multiple cancer risk factors have shown great promise, [25-27], and a variety of approaches and settings have been utilized to address multiple cancer risk factors. For example, both worksite and health center based multiple risk factor interventions have shown efficacy with respect to improving diet and physical activity, but smoking cessation results have generally not been as positive [25,26,106-109]. Overall, multiple risk factor interventions provide an exceptionally promising and efficient means by which to facilitate behavior change and reduce cancer risk. Further, telephone-based interventions have demonstrated efficacy and broad reach as a method of of delivering smoking cessation, physical activity and diet/nutrition interventions [30-34]. The proposed study builds on this work using an intervention approach that has already been proven effective addressing smoking [30]. This intervention will be adapted, through literature review, expert consultation, and qualitative work, to simultaneously address smoking cessation, fruit/vegetable consumption, and physical activity, and to be sensitive to the needs of the target population. To the best of our knowledge, the current study will be among the first multiple risk factor intervention studies to focus on Mexican-origin individuals in general, and more specifically on overweight/obese Mexican-origin smokers, an extremely high risk group.

MAPS combines two widely utilized and empirically validated approaches [36,39] into a comprehensive, proactive, holistic approach that is specifically tailored to the motivational state, life concerns, and needs/preferences of the target population. MAPS is built around an individualized “wellness program” that is based on both successful chronic care models, patient navigation programs, and feedback from underserved communities. In addition to providing the necessary long-term support and strategies to initiate and maintain change, such an approach could potentially be more cost-effective than shorter interventions because of its effects on increasing the durability of treatment effects. Despite enthusiasm for more chronic care type approaches to behavior change, there have been few attempts to actually develop such programs. Moreover, telephone-based multiple risk factor counseling can both reduce the total number of risk factors, and be most effective among individuals with the greatest risk i.e., among individuals with larger numbers of risk factors; [26]. Further, treating cancer risk factors within a chronic care model, as MAPS does, has the potential to boost long-term success rates by improving the ability of an intervention to promote motivation, aid change attempts, prevent relapse, and encourage recycling among individuals who are unsuccessful [110-113].
